## Abstract

**Background:**

Blood pressure (BP) is poorly controlled among a large proportion of hypertensive outpatients. Innovative models of care are therefore needed to improve BP control. The Team-Based Care for improving Hypertension management (TBC-HTA) study aims to evaluate the effect of a team-based care (TBC) interprofessional intervention, involving nurses, community pharmacists and physicians, on BP control of hypertensive outpatients compared to usual care in routine clinical practice.

**Methods/design:**

The TBC-HTA study is a pragmatic randomized controlled study with a 6-month follow-up which tests a TBC interprofessionnal intervention conducted among uncontrolled treated hypertensive outpatients in two ambulatory clinics and among seven nearby community pharmacies in Lausanne and Geneva, Switzerland. A total of 110 patients are being recruited and randomized to TBC (TBC: *N* = 55) or usual care group (UC: *N* = 55). Patients allocated to the TBC group receive the TBC intervention conducted by an interprofessional team, involving an ambulatory clinic nurse, a community pharmacist and a physician. A nurse and a community pharmacist meet patients every 6 weeks to measure BP, to assess lifestyle, to estimate medication adherence, and to provide education to the patient about disease, treatment and lifestyle. After each visit, the nurse and pharmacist write a summary report with recommendations related to medication adherence, lifestyle, and changes in therapy. The physician then adjusts antihypertensive therapy accordingly. Patients in the UC group receive usual routine care without sessions with a nurse and a pharmacist. The primary outcome is the difference in daytime ambulatory BP between TBC and UC patients at 6-month of follow-up. Secondary outcomes include patients’ and healthcare professionals’ satisfaction with the TBC intervention and BP control at 12 months (6 months after the end of the intervention).

**Discussion:**

This ongoing study aims to evaluate the effect of a newly developed team-based care intervention engaging different healthcare professionals on BP control in a primary care setting in Switzerland. The results will inform policymakers on implementable strategies for routine clinical practice.

**Trial registration:**

ClinicalTrials.gov registration: NCT02511093. Retrospectively registered on 28 July 2015.

## Background

High blood pressure (BP) is a major risk factor for cardiovascular diseases (CVD) and mortality worldwide [1]. Although treatment of hypertension can substantially reduce this risk, hypertension remains underdected, undertreated, and poorly controlled [2, 3]. For example, half of North American treated patients with hypertension remain uncontrolled [4, 5]. A similar proportion has been found in Switzerland [6]. Furthermore, due to ageing populations, busy clinical workloads, and shortage of physicians in most healthcare systems, new approaches to hypertension care, involving pharmacists [7, 8] or nurses [9, 10], could be a promising approach to improve BP management and control.

Pharmacists are highly accessible healthcare professionals and indeed a valuable asset to improve hypertension management by providing medication management in collaboration with physicians and by supporting patients in medication intake [11–14]. Evidence supports that pharmacists – working alone or in teams – are effective for the management of hypertension [13, 15–17] and other CVD risk factors [16, 18, 19]. Nurses, by providing lifestyle counseling and health education, are also helpful for the management chronic diseases [20, 21], including hypertension [9, 22–24]. They are a valuable member of team-based care at the interface between patients and physicians [25]. Furthermore, nurses can also intervene in collaboration with pharmacists to improve BP as shown in a Canadian study and in community-based prevention programs in Canada and in the USA [26–30]. Santschi et al. demonstrated that a collaborative model involving community pharmacists and primary care physicians focused on the management of drug adherence was feasible in the Swiss healthcare system [31] and improved long-term BP control among uncontrolled hypertensive patients [32].

Team-based care is a coordinated model of care involving different healthcare professionals, such as physicians, pharmacists, nurses or other non-physician clinicians, working in a collaborative partnership, each with their own expertise [18, 25, 27]. Team-based care of hypertension has recently been recommended by the U.S Community Preventive Services Task Force [33, 34]. To this day, a team-based care, involving nurses and community pharmacists working in collaboration with physicians, to improve BP control need to be evaluated in European countries, and in particular in Switzerland.

Therefore, we launched the Team-Based Care for improving Hypertension management (TBC-HTA) randomized controlled study. This study is designed to evaluate if a TBC interprofessional intervention, involving nurses and community pharmacists working in collaboration with physicians, improves BP control among uncontrolled treated hypertensive patients under real-life conditions.

## Methods/design

### Study design and setting

The TBC-HTA study is an ongoing 3-year multicenter pragmatic randomized controlled trial comparing a 6-month team-based care interprofessional intervention, involving nurses, community pharmacists and physicians, to a usual care group among 110 outpatients followed in ambulatory clinics and their nearby community pharmacies in Lausanne and Geneva areas, Switzerland (Fig. 1). The patient is the unit of randomization and the unit of analysis. We applied a pragmatic approach to determine the effect of the TBC intervention under real-life conditions with existing community healthcare professional resources [35].

**Fig. 1 Fig1:**
[figure not shown]
Study Flow Diagram

Treated uncontrolled hypertensive outpatients followed in ambulatory clinics are recruited and randomly allocated to one of two groups: 1) the TBC intervention group (TBC: *N* = 55), in which patients receive care from nurses and community pharmacists working in collaboration with physicians; 2) the usual care group (UC: *N* = 55) in which patients receive routine care without any intervention from nurses or community pharmacists. Patients are recruited from two ambulatory clinics: 1) the Hypertension Clinic, an outpatient clinic affiliated with Lausanne University Hospital (CHUV; www.chuv.ch) and located in Lausanne, 2) Cité générations, an ambulatory care center located in Geneva (www.cite-generations.ch). Regular staff nurses and physicians of the Hypertension Clinic and Cité Générations are involved in the study. Nearby community pharmacists in Lausanne and Geneva are recruited based on their geographical proximity to the ambulatory clinics to facilitate the follow-up of patients.

### Participants

#### Identification and recruitment

Patients with the following inclusion criteria are eligible to participate: 1) uncontrolled hypertension [defined as daytime systolic ambulatory blood pressure measurement (ABPM) ≥135 and/or diastolic ABPM ≥85 mmHg or office systolic BP ≥140 and/or office diastolic ≥90 mmHg over at least two consecutive visits [36]]; 2) taking at least one antihypertensive medication; 3) aged 18 years old or more; 4) speak and understand French; and 5) agree to use the service from the same pharmacy for the duration of the study. Patients are excluded if they 1) are unable to understand the study aim; 2) are pregnant or lactating; 3) live in a nursing home; 4) are hospitalized; 5) participate in another study; or 6) have daytime 24-h ABPM > 180/110 mmHg. Eligible patients are contacted by phone by a nurse who explains the study and ascertains the patient’s willingness to participate. If the patient agrees to participate, the study information material is sent and an appointment is scheduled by the nurse at the ambulatory clinics. After consenting and completing the baseline assessment, patients are randomized in a 1:1 allocation ratio to the TBC intervention group or to the UC care group.

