### TBC intervention

The TBC interprofessional intervention, based on distinct competencies of healthcare professionals involved in hypertension care, comprises:A 2-h training workshop during which nurses and community pharmacists are trained about the study requirements, standardized BP measurement and hypertension care according to the European Society of Hypertension recommendations [36], antihypertensive medication management (including the assessment of medication adherence), and counseling about lifestyle modification (physical activity and diet);Structured individual sessions conducted by ambulatory clinic nurses at baseline, 6, 12 and 18-week and structured individual sessions conducted by community pharmacists at baseline, 6, 12 and 18-week. Specifically, at each session, the nurse measures BP, estimates adherence using the Morisky Medication Adherence Scale (MMAS-8) [37, 38], and provides lifestyle counseling (physical activity and diet) during structured face-to-face interviews with the patient. After each session, the nurse sends a summary report (outlining BP measurements, score of MMAS-8, physical activity and diet assessment with any counselling and recommendations) is sent by fax to the pharmacist. The physician has access to this report. The patient is then referred to the community pharmacist who measures BP and emphasizes medication adherence with the patient (using a specified guide following a step process: gathering information from the patient, creating a medication list, and identifying drug related problems) during each structured individual session. After each session, the pharmacist sends a summary report (outlining BP measurement, score of MMAS-8, and any recommendations to change treatment) by fax to the nurse. The physician has access to this report.

No medication change is allowed during the first 6 weeks of follow-up. If BP is uncontrolled (≥140/90 mmHg) at the 6, 12 and 18-week session with the community pharmacist or the nurse, a contact (by phone or face-to-face) with the physician is made by the nurse. Taking account of the nurses’ and community pharmacists’ recommendations on lifestyle, medication adherence, and therapy, the physician adapts the treatment if necessary.

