### Blood pressure measurement

At each visit, BP is measured in TBC patients by the nurse and the community pharmacist using the clinically validated Microlife WatchBP home oscillometric device [39], using a standardized protocol. At the end of the 6-month follow-up, ABPM is performed among TBC and UC patients using the clinically validated electronic Diasys device (DIASYS integra; Novacor SA, Rueil-Malmaison, France) [40]. The ABPM device is installed on the dominant arm by the nurse who explains the procedure to the patient. Measurements are based on the auscultatory mode, relayed by the oscillometric mode in case of failure of the auscultatory mode. Measurements are made every 20-min intervals during the day and every 60-min intervals during the night [36]. The mean daytime ABPM is calculated from the average of BP readings obtained between 9.30 am to 9.30 pm.

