### Outcomes

The primary outcomes are 1) the difference in mean daytime ABPM at 6-month between TBC and UC patients and 2) the difference in the proportion of patients with controlled BP (daytime ABPM <135/85 mmHg) at 6-month between TBC and UC patients. Secondary outcomes include 1) patient’s and healthcare professionals’ satisfaction with the TBC intervention (using specified questionnaires administered at the end of the follow-up); 2) the difference in the proportion of TBC and UC patients with controlled BP (daytime ABPM <135/85 mmHg) at 12 months (6 months after the end of the intervention).

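### Patients can enter on office BP alone while control is judged on daytime ABPM, so some may already count as controlled at baseline, which can dilute the control-proportion comparison and blurs what the 6-month rate means

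*Protocol article*

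**What the plan says.** Under Identification and recruitment, there are two routes into the trial. One is "daytime systolic ambulatory blood pressure measurement (ABPM) ≥135 and/or diastolic ABPM ≥85 mmHg". The other, which suffices on its own, is "or office systolic BP ≥140 and/or office diastolic ≥90 mmHg over at least two consecutive visits". The only exclusion that uses ABPM is an upper limit: patients who "have daytime 24-h ABPM > 180/110 mmHg".

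Under Outcomes, both primary outcomes use ABPM alone: "the difference in mean daytime ABPM at 6-month between TBC and UC patients" and "the difference in the proportion of patients with controlled BP (daytime ABPM <135/85 mmHg) at 6-month between TBC and UC patients". The 12-month secondary outcome uses the same control definition.

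Under Blood pressure measurement, ABPM is described at one time point: "At the end of the 6-month follow-up, ABPM is performed among TBC and UC patients". No baseline ABPM is described there.

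Under Statistical analyses, the month-6 means are compared by a t-test and the control proportions by a chi-squared test. Regression is added to deal with possible imbalances between groups, and its covariates are not named. Under Sample size, the trial is sized on systolic BP only, with no allowance for entrants already below the ABPM threshold.

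**The concern.** Entry and success are defined on different scales. A patient with raised office BP on two visits and a daytime ABPM of, say, 128/80 mmHg enters as uncontrolled and is already a success by the second primary outcome. If nothing changes in six months, the chi-squared test counts that patient as controlled, in whichever arm.

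Two things are at stake. The first is interpretation: the trial asks whether team-based care brings uncontrolled patients under control, but the 6-month rate would mix patients who became controlled with patients who were never uncontrolled on that measure. The second is sensitivity: patients already below the threshold have little room to become newly controlled, so they raise the rate in both arms and can narrow the difference between them.

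**Working it through.** **1. Can it happen on the text?** Yes. The two entry routes are joined by *or*, the ABPM exclusion has no lower limit, and the control outcome uses ABPM only. How often it happens cannot be derived: the article gives neither the share of such entrants (call it w) nor any expected control rate.

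**2. The plan's own figure.** Inputs from Sample size: difference 6 mmHg, SD 10 mmHg, two-sided 5%, power 80%, dropout about 15%.
- Normal approximation: n = 2 × [10 × (1.960 + 0.842) / 6]² = 2 × 4.670² = 43.6, so 44 per group.
- With the t distribution, 45 per group are needed, and power at the stated 46 is 81%.
- Dropout: 46 / 0.85 = 54.1, rounded up to 55.

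The stated 46 and 55 are sound for the mean. No calculation is given for the control proportion.

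**3. Control proportion.** Assumed, not from the article: among patients uncontrolled on ABPM at baseline, 25% (usual care) and 48% (team-based care) are controlled at 6 months; among those already controlled, 80% in both arms.

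Rate in each arm: p = (1 − w) × p(uncontrolled) + w × 0.80. The difference is therefore (1 − w) × 23 points.

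Power = Φ{[d − 1.96 × √(2p̄(1 − p̄)/n)] / √([p₁(1 − p₁) + p₂(1 − p₂)]/n)}, with n = 46.

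At w = 20%: p₁ = 0.8 × 0.25 + 0.16 = 0.360; p₂ = 0.8 × 0.48 + 0.16 = 0.544; d = 0.184; p̄ = 0.452. The standard errors are 0.1038 and 0.1020. Power = Φ[(0.184 − 0.2034) / 0.1020] = Φ(−0.19) = 42%.

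| w | Usual care | Team-based care | Difference | Power |
|---|---|---|---|---|
| 0% | 25.0% | 48.0% | 23.0 points | 63% |
| 20% | 36.0% | 54.4% | 18.4 points | 42% |
| 30% | 41.5% | 57.6% | 16.1 points | 34% |

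With more favourable assumed rates of 30% and 60%, the difference goes from 30 to 24 to 21 points and power from 84% to 64% to 53%. Changing the 80% to 70% or 90% with these rates hardly alters the result.

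**4. Mean systolic ABPM.** Let e be the effect in patients already controlled on ABPM. The average effect is 6(1 − w) + e × w. Power is from the t-test, 46 per arm, SD held at 10 mmHg, w = 20%.

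| Effect elsewhere | e | Average effect | Power |
|---|---|---|---|
| 6 mmHg | 0 | 4.8 mmHg | 62% |
| 6 mmHg | 3 mmHg | 5.4 mmHg | 73% |
| 6 mmHg | 6 mmHg | 6.0 mmHg | 81% |
| 10 mmHg | 0 | 8.0 mmHg | 97% |

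The mean can thus lose a good deal or nothing, depending on a quantity that the article does not give.

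**5. What a restricted analysis recovers.** Among patients above the ABPM threshold at baseline, the 23-point difference is intact but n falls to 46 × (1 − w). At w = 20% that is about 37 per arm and 54% power (against 42%); at w = 30%, about 32 per arm and 48% (against 34%). It recovers part of the loss and never reaches the 63% seen at w = 0.

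**The case against.** A reader might infer that both primary comparisons are diluted. The article does not support that for mean ABPM. Every patient in the intervention arm receives the nurse and pharmacist sessions, and physician contact depends on session readings, not on ABPM: "If BP is uncontrolled (≥140/90 mmHg) at the 6, 12 and 18-week session with the community pharmacist or the nurse". A patient with high office BP and normal ABPM can therefore still have treatment changed and ABPM lowered. Nor is the 6 mmHg stated to be the effect in ABPM-uncontrolled patients only. It is the low end of an expected 6 to 10 mmHg between the groups as randomized.

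A reader might also infer bias between arms. There is none: allocation is random within each clinic, so such patients fall in both arms by chance alone.

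A third inference is that the ABPM-uncontrolled subset should become the primary population. That would change the question. The article defines uncontrolled to include the office route, calls the trial pragmatic and commits to intention-to-treat. The subset would also cut n by the fraction w.

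It is fair, too, that the rates in step 3 are assumed, and that power there is only 63% with w = 0, so the entry rule does not explain all of the weakness. Finally, the article already describes baseline BP by arm and plans regression, and covariate lists usually belong in an analysis plan. This last objection stands only in part. The article fixes unadjusted tests as the main comparisons and keeps regression for imbalances. That choice is stated, not left open.

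**Conclusion.** The mismatch between entry and control outcome is real on the text and worth correcting, but its scope is limited. It affects the control proportion: the 6-month rate is hard to interpret, and the difference shrinks in proportion to 1 − w if already-controlled patients do equally well in both arms. Under the assumed 25% and 48% (80% in both arms otherwise), power at 46 per arm falls from 63% to 42% at w = 20% and 34% at w = 30%. For mean ABPM, power at w = 20% lies between 62% and 81% as the effect in these patients runs from none to the full 6 mmHg, so a loss is possible but not shown. The arms are not biased. The share w and all control rates are assumptions; only the trial's own baseline data can settle the size.

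**What to change.** - Keep all randomized patients as the primary intention-to-treat population. Do not make the ABPM-uncontrolled subset primary.
- Under Statistical analyses, replace the t-test and chi-squared test as main analyses with linear and logistic models adjusted for baseline daytime ABPM and for clinic, by which the randomization lists are separated. Adjustment takes account of where each patient started. It does not restore the diluted difference in proportions, and its gain in precision cannot be computed from the article, which gives no correlation between baseline and 6-month ABPM.
- Report, by arm, the share of patients with baseline daytime ABPM below 135/85 mmHg.
- Prespecify a sensitivity analysis of the control outcome among patients with baseline daytime ABPM ≥135 and/or ≥85 mmHg. This group is defined before randomization, so the comparison within it remains randomized.
- Under Blood pressure measurement, state that daytime ABPM is recorded at baseline for every patient. The upper-limit exclusion implies such a measurement, but the section describes ABPM only at the end of follow-up. The adjusted models and the sensitivity analysis depend on it.

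The cost is some additional analysis work and a smaller n in the sensitivity analysis. Entry criteria and sample size stay as they are.

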### TBC intervention

The TBC interprofessional intervention, based on distinct competencies of healthcare professionals involved in hypertension care, comprises:A 2-h training workshop during which nurses and community pharmacists are trained about the study requirements, standardized BP measurement and hypertension care according to the European Society of Hypertension recommendations [36], antihypertensive medication management (including the assessment of medication adherence), and counseling about lifestyle modification (physical activity and diet);Structured individual sessions conducted by ambulatory clinic nurses at baseline, 6, 12 and 18-week and structured individual sessions conducted by community pharmacists at baseline, 6, 12 and 18-week. Specifically, at each session, the nurse measures BP, estimates adherence using the Morisky Medication Adherence Scale (MMAS-8) [37, 38], and provides lifestyle counseling (physical activity and diet) during structured face-to-face interviews with the patient. After each session, the nurse sends a summary report (outlining BP measurements, score of MMAS-8, physical activity and diet assessment with any counselling and recommendations) is sent by fax to the pharmacist. The physician has access to this report. The patient is then referred to the community pharmacist who measures BP and emphasizes medication adherence with the patient (using a specified guide following a step process: gathering information from the patient, creating a medication list, and identifying drug related problems) during each structured individual session. After each session, the pharmacist sends a summary report (outlining BP measurement, score of MMAS-8, and any recommendations to change treatment) by fax to the nurse. The physician has access to this report.

No medication change is allowed during the first 6 weeks of follow-up. If BP is uncontrolled (≥140/90 mmHg) at the 6, 12 and 18-week session with the community pharmacist or the nurse, a contact (by phone or face-to-face) with the physician is made by the nurse. Taking account of the nurses’ and community pharmacists’ recommendations on lifestyle, medication adherence, and therapy, the physician adapts the treatment if necessary.

### Usual care group

Patients in the UC group received routine care by their usual physician without nurse or community pharmacist intervention.

### Blood pressure measurement

At each visit, BP is measured in TBC patients by the nurse and the community pharmacist using the clinically validated Microlife WatchBP home oscillometric device [39], using a standardized protocol. At the end of the 6-month follow-up, ABPM is performed among TBC and UC patients using the clinically validated electronic Diasys device (DIASYS integra; Novacor SA, Rueil-Malmaison, France) [40]. The ABPM device is installed on the dominant arm by the nurse who explains the procedure to the patient. Measurements are based on the auscultatory mode, relayed by the oscillometric mode in case of failure of the auscultatory mode. Measurements are made every 20-min intervals during the day and every 60-min intervals during the night [36]. The mean daytime ABPM is calculated from the average of BP readings obtained between 9.30 am to 9.30 pm.

